### Randomization

Randomization of participants will take place after parental consent and first assessments. The infants will be randomized into two groups: 1) control group (conventional guidelines) and 2) experimental group (STEP protocol, using an electronic allocation system (www.sealedenvelope.com). The person responsible for generating and controlling the randomization list will be the only person with access to that list, and will not participate in any other part of the study. The list will be stored on the randomization website and can only be consulted by password.

Children will be allocated to the group by randomization in blocks of 6, with a 1: 1 allocation rate. A person responsible for the randomization list will inform the person responsible for the intervention the assigned group, through a sealed envelope containing the group’s information.

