### Study design

This is a randomized, controlled, parallel, single-blind clinical study. The allocation rate will be 1: 1. The clinical study protocol was based on the Standard Protocol Items: Recommendations for Intervention Trials - SPIRIT guide [23]. This study was registered in the “REBEC” (Brazilian database for the registration of clinical trials) (registration number: RBR-8xrzjs - Available in http://www.ensaiosclinicos.gov.br/rg/RBR-8xrzjs/ - Issue date: 15 Aug 2021; Protocol amendment number: 02) and will follow the standards established by CONSORT [24].

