### Sample size

The study will have a non-probabilistic convenience sample. The sample calculation was performed a priori using the G*Power software. Sample size was determined based on the data obtained in the study by Hielkema [25], from the total score of the Infant Motor Profile (IMP) scale. An effect size of 0.23, statistical power of the test of 90% and statistical significance of 5% were considered. The sample calculation resulted in 52 participants. To guarantee a sufficient number of participants, the inclusion of 15% more participants was established in order to meet a possible dropout rate. Thus, the allocation of 30 participants in each group was determined.

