### Blinding

Therapists responsible for conducting assessments will be blinded to group allocation. The persons that will score the assessments are not the same as those that conduct the assessments or the intervention. They will be blind to group allocation by analysing coded videos. Also, the person responsible for data and statistics analysis will be blind. For methodological reasons and due to the nature of the interventions, it will not be possible to blind the therapists that will perform the interventions.

The allocation will not be disclosed to the patient/parents, the therapist from the other group, the evaluators and other research participants.

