### Intervention

Therapists responsible for the application of the experimental STEP protocol will receive standardized training consisting of: a) strategies to determine the best activities to be included in the intervention; b) improving and enriching the environment, c) how to guide parents to encourage infant participation at home, with family and in the community; f) components of interaction and how to improve the parent-child interaction. Each group will have its own therapist, and the therapists will not know information about the participants and the progress of the other group. Therapists providing control group intervention will not be aware of the content of the experimental intervention and will receive standardized training.

In both groups, participants will be free to access additional therapy (in person or online) to that offered by this study. In the case of any additional therapy, data on the type of therapy, frequency and duration will be collected. The total dose of therapies will be added as a covariate in the statistical analysis.

To encourage caregivers to continue the study and carry out all stages of evaluations and interventions, reports on the infant’s development will be delivered to the caregiver, to assist in the knowledge about the child’s development and needs. The main principles and differences between the intervention applied in the two groups are shown in Table 1.

**Table 1 Tab1:** Main principles and differences of intervention between groups

Intervention		
	Control Group	Step Protocol
**Elements**	• Standard functional tasks performed at home by parents to stimulate motor capacity.	• Goals established with parents, through the GAS scale. • Functional tasks performed at home by parents to stimulate motor capacity; • Stimulation of participation at home; • Stimulation of parent-infant interaction; • Environmental enrichment.

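### A single, published block size of 6 leaves a small, avoidable risk that some allocations can be deduced; concealed varying sizes would remove most of that certainty

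*Protocol article*

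**What the plan says.** Under Randomization, the article prescribes "randomization in blocks of 6, with a 1: 1 allocation rate". It gives one size and mentions neither variation nor concealment of it. Study design confirms the ratio: "The allocation rate will be 1: 1". Under Sample size, "the allocation of 30 participants in each group was determined", so 60 infants fill ten blocks. No stratification factor is named.

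On who learns the allocation, Randomization says: "A person responsible for the randomization list will inform the person responsible for the intervention the assigned group", by sealed envelope. Blinding says that "it will not be possible to blind the therapists that will perform the interventions". Intervention adds: "Each group will have its own therapist, and the therapists will not know information about the participants and the progress of the other group".

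The article also sets out safeguards:
- The person who generates and controls the list "will be the only person with access to that list, and will not participate in any other part of the study" (Randomization).
- Randomisation comes after consent and the first assessments (Randomization).
- Allocation is not disclosed to parents, the other group's therapist, the evaluators or other participants (Blinding).
- Scoring is done from coded videos by people who neither conduct the assessments nor deliver the intervention (Blinding).

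**The concern.** With one known block size, a block becomes transparent once either arm has received its three infants: every remaining place belongs to the other arm. Keeping the list under password protects the list itself. It does not prevent this deduction, which needs only the past allocations and the position in the block.

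Each therapist sees one arm only. In a two-arm trial, however, a therapist who also knows how many infants have been randomised obtains the other arm's count by subtraction. The article does not say that the running count or the enrolment order is withheld from therapists, or that those who enrol infants cannot see past allocations.

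At stake are allocation concealment at entry, where knowing the next slot could influence whether or when an infant is enrolled, and, more remotely, the blinding of those who run the assessments.

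**Working it through.** **Inputs.** Block size 6 and ratio 1:1, so 3 + 3 per block (Randomization; Study design). Number randomised: 2 × 30 = 60 (Sample size), consistent with the article's 52 plus 15%: 52 × 1.15 = 59.8, rounded up to 60. Blocks: 60 / 6 = 10. The article gives no figure for predictability, so there is none to reproduce.

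**Assumption for the upper bound.** The observer knows all earlier allocations in order, and where each block starts.

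**Certain allocations per block.** There are C(6,3) = 20 equally likely orders. An allocation is certain when one arm already has its three.

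| Position in block | 1 | 2 | 3 | 4 | 5 | 6 |
|---|---|---|---|---|---|---|
| Probability already certain | 0 | 0 | 0 | 0.10 | 0.40 | 1.00 |

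The sum is 0.10 + 0.40 + 1.00 = 1.5 of 6, or 25%. The closed form agrees: for a block of 2m, the expected number certain is 2m/(m + 1); with m = 3 this is 6/4 = 1.5, a share of 1/(m + 1) = 1/4.

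**Whole trial.** 10 × 1.5 = 15 of 60 expected. Each block has 1, 2 or 3 certain places with probability 0.6, 0.3 and 0.1. Over ten blocks the central 95% range is 11 to 19, with a minimum of 10 and a maximum of 30.

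**Best-guess success.** The observer always names the arm with more places left. The success probabilities by position are:
- 1st: 0.5
- 2nd: 3/5 = 0.6
- 3rd: 0.6 × 0.5 + 0.4 × 0.75 = 0.6
- 4th: 0.1 × 1 + 0.9 × 2/3 = 0.7
- 5th: 0.4 × 1 + 0.6 × 0.5 = 0.7
- 6th: 1.0

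The total is 4.1, and 4.1 / 6 = 68.3%, against 50% under simple randomisation.

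**Effect of varying the size.** Simulation, 4,000 trials of 60 per row. The observer knows the full history and the set of possible sizes, but not the sizes drawn.

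| Block sizes | Certain allocations | Best-guess success |
|---|---|---|
| 6 only | 25.0% | 68.3% |
| 4 or 6 | 5.5% | 69.0% |
| 4, 6 or 8 | 2.3% | 67.8% |

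Varying the size removes most of the certainty. It hardly changes the average guessing rate.

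**The case against.** The strongest reply is that the 25% describes an observer whom the article does not provide. The full ordered history lies with one person who has no other task in the study, and allocations are withheld from evaluators, parents and the other arm's therapist. This largely stands. It makes 25% an upper bound. It does not bring the risk to zero, because enrolment order and running count are not stated to be withheld.

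Four stronger readings are tempting, and the article does not support them.

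- **That a quarter of this trial's allocations are in fact predictable.** This would need someone with the complete history. Nothing in the article says that therapists receive the order or the count.
- **That selection bias at entry is shown.** No section gives intervention therapists a part in recruitment, eligibility or consent. Randomisation after consent and baseline assessment further narrows the opening. A route is possible but not demonstrated.
- **That the primary outcomes lose their blinding.** A parent who describes the programme to an evaluator reveals that infant's arm whatever the block size. To deduce another infant's arm with certainty, the evaluator would need three known same-arm allocations in one identified block. The evaluator does guide the filmed motor assessments live, so evaluator blinding has some value, but separate people score the coded recordings.
- **That varying sizes would cure the 68% guessing rate.** The simulation shows that they would not.

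It can also be said that fixed blocks under independent custody are an accepted design. That is fair: nothing here is a contradiction or a miscalculation.

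**Conclusion.** The point stands as a cheap improvement. The single block size, its publication and the unblinded, arm-specific therapists are all in the text. The 25% (about 15 of 60) is exact as an expectation, conditional on knowing the earlier allocations and the enrolment order, with blocks filled in sequence and no stratification. Under the safeguards described, actual exposure should be well below that; the article gives no basis for a figure. What remains is a small risk that can be avoided at little cost.

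**What to change.** For any infants not yet randomised, the list holder should generate the list with randomly varying block sizes, for example 4, 6 and 8. The sizes should be known only to the list holder and kept out of study documents until recruitment ends. The protocol should also state that those who enrol or assess infants do not see past allocations, and that therapists are not given the enrolment order or running count.

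The benefit is a fall in certain allocations from 25% to roughly 2% to 6% for a fully informed observer. The cost is regenerating the remaining list and accepting a possible final imbalance: if recruitment stops in the middle of a block of 8, the arms can differ by at most 4 infants (32 against 28).

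The article does not give recruitment status, and the change cannot make infants already allocated less predictable. If recruitment has finished, the trial report can state who knew the block size and who had access to earlier allocations.

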### Blinding

Therapists responsible for conducting assessments will be blinded to group allocation. The persons that will score the assessments are not the same as those that conduct the assessments or the intervention. They will be blind to group allocation by analysing coded videos. Also, the person responsible for data and statistics analysis will be blind. For methodological reasons and due to the nature of the interventions, it will not be possible to blind the therapists that will perform the interventions.

The allocation will not be disclosed to the patient/parents, the therapist from the other group, the evaluators and other research participants.

### Intervention

Therapists responsible for the application of the experimental STEP protocol will receive standardized training consisting of: a) strategies to determine the best activities to be included in the intervention; b) improving and enriching the environment, c) how to guide parents to encourage infant participation at home, with family and in the community; f) components of interaction and how to improve the parent-child interaction. Each group will have its own therapist, and the therapists will not know information about the participants and the progress of the other group. Therapists providing control group intervention will not be aware of the content of the experimental intervention and will receive standardized training.

In both groups, participants will be free to access additional therapy (in person or online) to that offered by this study. In the case of any additional therapy, data on the type of therapy, frequency and duration will be collected. The total dose of therapies will be added as a covariate in the statistical analysis.

To encourage caregivers to continue the study and carry out all stages of evaluations and interventions, reports on the infant’s development will be delivered to the caregiver, to assist in the knowledge about the child’s development and needs. The main principles and differences between the intervention applied in the two groups are shown in Table 1.

**Table 1 Tab1:** Main principles and differences of intervention between groups

Intervention		
	Control Group	Step Protocol
**Elements**	• Standard functional tasks performed at home by parents to stimulate motor capacity.	• Goals established with parents, through the GAS scale. • Functional tasks performed at home by parents to stimulate motor capacity; • Stimulation of participation at home; • Stimulation of parent-infant interaction; • Environmental enrichment.
**Materials**	• The therapist responsible for the intervention will be trained and will receive a manual with all the motor activities that can be given to the infant, and how to explain each activity to the parents. • Caregivers will receive a booklet with all the functional activities they should perform with the infant, with instructions on how to perform, how many repetitions, which position and what stimuli should be given to elicit the activity.	• The therapist responsible for the intervention will be trained and will receive a manual with all the motor activities that can be given to the infant, and how to explain each activity to the parents. • Caregivers will receive a booklet with all the functional activities they should perform with the infant. The activities will be customized for each infant in the group, according to the skills presented in the assessment and the goals established with parents by the GAS scale. The booklet will have instructions on how to perform each activity, how many repetitions, which position and what stimuli should be given to elicit the activity. • Caregivers will receive a booklet with the main aspects of participation that should be inserted in the infant’s routine, based on the analysis of the participation of each infant. • Caregivers will receive an illustrative manual on the interaction with the infant, covering the main aspects of an adequate interaction, based on the analysis of the facilitators and barriers to interaction, for each infant. • Caregivers will receive instructions on which toys are suitable for the infant’s age, appropriate to the family’s context
**Where?**	• The intervention will take place in the family’s home environment. Parents will be instructed on how to maintain the proper environment (safe, free from external stimuli, with appropriate toys).	• The intervention will take place in the family’s home environment. Parents will be instructed on how to maintain the proper environment (safe, free from external stimuli, with appropriate toys).
**Who executes it?**	• The infants’ parents will carry out the activities. They will receive online guidance from the therapists on all the details of the intervention. • Parents will have a weekly meeting with the responsible therapist to ask questions, check on the infant’s progress, and ensure that the intervention is being carried out with quality.	• The infants’ parents will carry out the activities. They will receive online guidance from the therapists on all the details of the intervention. • Parents will have a weekly meeting with the responsible therapist to ask questions, check on the infant’s progress, and ensure that the intervention is being carried out with quality. • Parents will define with the therapist the goals to be achieved through the GAS scale.
**Dose**	• Motor activities will be performed 30 min a day, 5 days a week.	• Motor activities will be performed 30 min a day, 5 days a week. • The parent-infant interaction + participation will not be measured, but parents will be encouraged to include these aspects in their daily routine.
**Fidelity**	• Parents will record in a pre-determined worksheet everything that was accomplished in each daily session. Afterwards, the therapist will follow the records weekly to see if the parents are following the guidelines exactly.	• Parents will record in a pre-determined worksheet everything that was accomplished in each daily session. Afterwards, the therapist will follow the records weekly to see if the parents are following the guidelines exactly.

An example of the application of the control group protocol and the STEP protocol for the same infant is presented in Supplementary Table 1.

*Control group - conventional guidelines:* this group will receive guidance for the care and development of the infant in the home environment (carried out by the parents). These guidelines will not be specific to the context or the task, but they will have a general character, such as guidance for positioning the infant, stimulation in different positions and general health care, following the guidelines for early stimulation for children aged 0 to 3 years with delay in neuropsychomotor development [29]. A simplified care diary will be provided to the caregiver, to record what the family has accomplished in terms of stimulation and recommended guidelines. The general guidelines and the care diary will be provided by therapists online.

Parents will be instructed to perform the activities for 30 min a day, 5 times a week, totaling 2:30 h of therapy per week. The distribution of therapy throughout the day will be carried out according to the needs and routine of the parents. Outcomes will be collected 10 weeks after baseline measurements.

*Experimental group – STEP protocol:* infants will practice goal directed task and context specific activities in the home environment (carried out by the parents), with assessment and instructions performed online. The protocol will last 10 weeks.

The home intervention will be performed by the parents. All instructions on carrying out the activities will be performed remotely, using the device chosen by the parents. The home practice will be organized according to 3 central principles: 1) establishment of goals; 2) practice of functional tasks and 3) guidance to parents (participation, parent-child interaction and environmental enrichment).

#### Establishment of goals

Initially, three functional objectives will be established according to the Goal Attainment Scale (GAS) [30]. The GAS consists of a measurement technique to quantify the progress of objectives and goals previously defined in an intervention program. The goals will be formulated according to SMART principles (Specific, Measurable, Achievable, Realistic and with a set Time). For each objective, an expected result will be stipulated, and a range of outcome possibilities above or below the expected will be applied. As the objectives are reached (0, + 1 or + 2 in GAS), there will be the establishment of new functional objectives, always maintaining 3 active objectives for the rehabilitation. The establishment of goals will happen after the evaluation of the basic measures and 5 weeks after the beginning of the interventions.

We emphasize that parents will be the main protagonists in setting goals, and the therapists responsible for the intervention will only direct caregivers according to the results of the baseline measurements. For that, a repertoire of possible functional goals will be developed and presented to parents, for the decision of which fit in the family context and the child’s motor capacity.

#### Functional tasks

The activities will be chosen according to the infant’s abilities, and the goals established together with parents. Thus, each family will receive an individualized intervention. The chosen activities will involve task-oriented training, functional activities according to capacities presented, and principles of motor learning. The repetition of each task, guidance on the choice and use of toys, use of sensory cues, identification of the infant’s attempts to produce active movements and self-regulate will be determined.

Parents will be taught by the therapist responsible for the intervention how to perform each activity with their child. Parents will also receive an online booklet, with a photo of each activity, position to be performed, explanation of how to perform the task, and means to stimulate the activity. After the parents receive the booklet with the activities, the therapist will call the parents (by phone or video call) to ensure that the parents understand how to carry out each activity and answer any questions.

Parents will be instructed to perform the activities for 30 min a day, 5 times a week, totaling 2:30 h of therapy per week. This will be the minimum recommended dose. If parents are able and choose to carry out a higher weekly dose of intervention, the researchers will collect data on how many hours per week the family carries out the guidelines. The distribution of therapy throughout the day will be carried out according to the needs and routine of the parents.

#### Guidance to parents

In addition to guidelines regarding functional activities, caregivers will receive recommendations on three topics: environmental enrichment, parent-child interaction and participation.Environmental enrichment: the researcher will advise parents on aspects of enriching the environment and guidance on the importance of contextual factors for the development of the infant, taking into account the socio-cultural conditions of each family. Aspects such as the arrangement of furniture, availability of toys, the presence of stimuli (noise, lighting) will be discussed in order to enrich the environment, optimizing the opportunities for learningParent- child interaction: Parents will receive an easy-to-read document with illustrations on how to increase the quality of interaction with their children. In this document, instructions on tone of voice, types of communication, importance of infant responses and cues, incentive for exploring objects, reciprocity in interaction, physical contact and other topics relevant to interaction will be given.Participation: This guidance will be developed according to the context of each family and the score on the YC-PEM scale regarding the child’s frequency and engagement at home. In general, parents will be guided in relation to the importance of including the infant in group activities at home, the importance of interacting with family members, in activities of interest to the child and family. The recommendations will also have the character of the infant’s participation at home, in activities such as mealtimes, hygiene and self-care.

An exact weekly time will not be determined for the completion of the above topics. However, we believe that changes in routine will have a significant impact on the stimulation time (participation, interaction) in addition to the time established for the daily activities mentioned.

Parental guidance will be conducted online and weekly. On this occasion, the therapist will hold a meeting by video transmission or telephone call. In this weekly contact, parents’ doubts, difficulties, perceptions of the infant’s improvement and possible suggestions will also be discussed.

